### Randomization and masking

2.6

Consented patients will be randomized to receive either CHM or placebo using concealed random allocation from a computer-generated random numbers table through the Dongfang hospital Clinical Research Institute. Once randomized, the patient will receive postoperative administration of either YLS or placebo after reperfusion of the culprit artery, as soon as possible. The treatment allocation will be concealed from the patient, the interventional cardiologist, the blinded research staff collecting the data and clinical endpoints, and other staff analyzing the outcome data.

The eligible consented patient will then be randomized to receive either:

1.CHM treatment: YLS will be administered as a granule (1 bag at a time, 2 times per day, 8 weeks). This dosing regimen is identical to that used in the other trials.^[20]^ Furthermore, this dose was also found to be cardioprotective in a preclinical model using animal.^[21]^2.Placebo control: Both YLS and placebo have the same outer packaging, color, shape, and flavor, so that neither the participant nor the investigator could recognize which group of intervention the participants are receiving before unblinding. After the treatment, the packaging will be returned to the investigators.

All patients will be transferred to the coronary care unit after the primary angiographic procedure. Intravenous glycoprotein IIb/IIIa inhibitor will be maintained for 18 to 36 hours after PCI. A loading dose of aspirin and P2Y12 inhibitors will be given before the procedure. An intravenous bolus of unfractionated heparin (100 U/kg) will be administrated right before the procedure to achieve therapeutic activated clotting time. Dual-anti-platelet therapy will be maintained during the deferred period and for at least 1 year after PCI. The peri-procedural treatment is in accordance with the Chinese guidelines for the management of AMI.^[22]^

### Sample size calculation

2.7

The formula used to calculate the sample size is as follows, which is based on superiority clinical trial hypothesis test sample size estimation.^[23]^ The sample size was calculated on the basis of expected reduction in NT-proBNP. One previous study suggested that the reducing value for NT-proBNP level in AMI patient treatment with PCI is 32%. Therefore, we assume the reduction in NT-proBNP level as 58% in this study. Given a type I error rate of α = 0.05, type II error rate of β = 0.2, Uα(0.05)=1.65, Uβ (0.2) =1.28. The sample size for 1 arm needs to be 63, resulting in n = 2 × 63 = 126 patients. Considering a dropout rate of 10%, a total of 138 patients need to be allocated to reach the required number of patients for the efficacy analysis. For convenience of randomization, we decided to recruit 140 patients. The formula used to calculate the sample size is as follows:$$\text{n1}={\left(\text{U}\alpha +\text{U}\beta \right)}^{2}\times 2P\times (1-P)/{\left(P1-P2\right)}^{2}=\text{n2}$$

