#### Primary and secondary outcomes

2.8.3

The primary outcome measures of the study are NT-proBNP and left ventricular ejection fraction, which will be measured at baseline and 8 weeks after randomization. Secondary outcomes include plasma levels of microRNA-145, plasma creatine kinase-MB, and CardiaC Troponin I levels in blood samples. At the same time, the trial also observes the occurrence of MACEs defined as the composites of deaths from any cardiac causes, myocardial infarction, and revascularization (PCI or CABG) at 8 weeks after randomization. The efficacy of angina symptoms, Seattle Angina Questionnaire, will be recorded at baseline and 8 weeks after randomization and TCM syndrome efficacy.^[24]^ Items to be measured and the time window of data collection are shown in Table 3.

**Table 3 T3:** Schedule of data collection.

Items	Screening period within 1 wk	Treatment period 4–8 wk	Follow-up period 2–12 mo
Signed informed consent	√		
Inclusion/exclusion criteria	√		
Demographic data	√		
Medical history, course of disease, treatment history	√		
Combined diseases	√		
Concomitant medications	√	√	
LVEF	√	√	
NT-proBNP	√	√	
microRNA-145	√		
CK-MB	√		
cTnI	√		
MACEs			√
SAQ	√	√	
TCM syndrome efficacy	√	√	
Vital signs	√	√	
Blood, urine and stool routine	√	√	
Liver and kidney function	√	√	
Adverse events		√	√

Vital signs: temperature, heart rates, breathing, and blood pressure.

CK-MB = creatine kinase-MB, cTnI = CardiaC Troponin I, LVEF = left ventricular ejection fraction, MACE = major adverse cardiac event, SAQ = Seattle Angina Questionnaire, TCM = Traditional Chinese Medicine.

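### The sample size puts 32% and 58% reductions in NT-proBNP level into a two-proportion formula, which matches neither the primary outcome nor the planned t test

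*Protocol article*

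**What the plan says.** Section 2.7 (Sample size calculation) of the protocol article says: "The sample size was calculated on the basis of expected reduction in NT-proBNP". The comparator figure comes from outside: "One previous study suggested that the reducing value for NT-proBNP level in AMI patient treatment with PCI is 32" (per cent). The figure for this trial is an assumption: "Therefore, we assume the reduction in NT-proBNP level as 58% in this study".

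The error rates and normal quantiles follow: "Given a type I error rate of α = 0.05, type II error rate of β = 0.2", with "Uα(0.05)=1.65, Uβ (0.2) =1.28". The printed formula is n1 = (Uα + Uβ)² × 2P(1 − P)/(P1 − P2)² = n2, and the result is: "The sample size for 1 arm needs to be 63, resulting in n = 2 × 63 = 126 patients". With 10% dropout and rounding, 140 are to be recruited.

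Section 2.8.3 (Primary and secondary outcomes) states: "The primary outcome measures of the study are NT-proBNP and left ventricular ejection fraction", both measured at baseline and 8 weeks. It sets no threshold of fall that would make a patient a responder. Section 2.11 (Statistical analyses) compares normally distributed data by independent-sample t test and names a Spearman test for the rest. It plans no comparison of proportions.

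**The concern.** The formula takes its variance, 2P(1 − P), from a yes/no outcome. A size of fall in a measured level is a different kind of number, even when it is written as a percentage. When two means are compared, the number of patients depends on the between-patient SD, and section 2.7 gives none.

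This is the only justification of the trial's size in the article. If the formula belongs to another endpoint and another test, the error rates attached to 63 per arm say nothing about the primary comparison. A null result on NT-proBNP could not then be read against a known power. The section also pairs β = 0.2 with a quantile that belongs to another power, so it is unclear even which power is claimed.

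**Working it through.** **Inputs from section 2.7:** P1 = 0.32, P2 = 0.58, Uα = 1.65, Uβ = 1.28. P is not printed; the average (0.32 + 0.58)/2 = 0.45 is used here.

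**Step 1: reproduce the plan's figure.**
- (1.65 + 1.28)² = 8.585
- 2 × 0.45 × 0.55 = 0.495
- (0.58 − 0.32)² = 0.0676
- n = 8.585 × 0.495 / 0.0676 = 62.86, rounded up to 63 per arm

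The stated 63 is reproduced, so the two percentages were used as binomial proportions.

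**Step 2: what the formula assumes about spread.** In a comparison of two means, n = (Uα + Uβ)² × 2 × SD²/difference². Matching terms, P(1 − P) stands where SD² should be. The imposed SD is √(0.45 × 0.55) = 0.497, about 50 percentage points. It is a by-product of the formula and does not come from NT-proBNP data.

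**Step 3: which error rates the 63 carries.** A normal quantile of 1.28 corresponds to β = 0.10 (90% power); β = 0.2 corresponds to 0.84. With 0.84 the same formula gives (1.65 + 0.84)² × 0.495 / 0.0676 = 6.200 × 0.495 / 0.0676 = 45.4, so 46 per arm. The 1.65 is the one-sided 0.05 value; two-sided 0.05 would use 1.96. Neither change repairs the mismatch in step 1, because the answer remains one for proportions.

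**Step 4: power for a comparison of means.** The calculation uses 63 per arm, a difference of 58 − 32 = 26 percentage points, and the t test with 124 degrees of freedom (non-central t). The SDs are assumptions, because the article gives none.

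| Assumed SD (points) | Power, two-sided 0.05 | Power, one-sided 0.05 |
|---|---|---|
| 40 | 95% | 98% |
| 50 | 83% | 90% |
| 60 | 67% | 78% |
| 70 | 54% | 67% |

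Both columns are shown because the section's own critical value is one-sided. The gap between columns is due to sidedness, and the fall down each column is due to the unstated SD. Power is at least 80% up to an SD of about 52 points (two-sided) or 58 points (one-sided).

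**Step 5: what 63 per arm detects.** By the normal approximation, two-sided 0.05 and 80% power give (1.96 + 0.84) × √(2/63) = 0.50 SD.

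**Step 6: log scale, if chosen.** If 32% and 58% are read as falls in the geometric mean, the ratio is 0.42/0.68 = 0.62, a log difference of 0.482. Two-sided 80% power with 63 per arm then needs a log-SD of at most about 0.96 (0.482 divided by the t-test detectable difference of 0.503).

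**The case against.** **The percentages may be responder rates.** The article never calls them means, and the source of the 32% is not at hand. If they were shares of patients reaching some target, the formula would suit them. This has some force: the wording points to a fall in level, but it does not prove it. The defect survives either reading. Responder rates would still be rates for an endpoint that section 2.8.3 does not define and section 2.11 does not analyse.

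**No shortfall is shown.** This stands. A reader might infer that the trial is underpowered, and the article does not support that. The result depends on an SD it does not give: below roughly 50 points 63 per arm is ample, and well above that it is too few.

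**The 63 might still deliver the claimed 80%.** A reader might treat 63 as the number for 80% power. Step 3 shows that it is not, even within the section's own formula.

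**The full protocol or an analysis plan may hold the proper calculation.** It may, but this is not an omission. The article prints the formula, the inputs and the result, and these do not fit the outcome.

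**A log-scale or baseline-adjusted justification is a reviewer's preference.** This also stands. Neither appears in section 2.11, so each is an option only, and would need a matching change there.

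**Conclusion.** The size justification is wrong as written and should be corrected. Section 2.7 sizes the trial with a two-proportion formula, while its primary outcome is a measured level with no responder definition and its planned comparison of normally distributed data is a t test. That holds however the 32% and 58% are read.

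The 63 per arm does not correspond to the stated β = 0.2, and it rests on a one-sided critical value that the text does not declare as such.

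The size of the consequence cannot be fixed from the article. Over assumed SDs of 40 to 70 points, power spans 95% to 54% two-sided, or 98% to 67% one-sided. These figures assume a true 26-point difference, equal SDs in the two arms and 63 evaluable patients per arm. The conclusion is that the stated power is not established; whether the true power is higher or lower is unknown.

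**What to change.** Keep 140 patients; at 10% dropout this leaves 140 × 0.9 = 126, or 63 per arm. Then rewrite section 2.7:

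1. Delete the proportions formula.
2. Justify the number for a difference in means of the NT-proBNP measure that section 2.11 will analyse, and say what the 32% and 58% represent.
3. State whether the test is one- or two-sided, and use a Uβ that matches the claimed power.
4. State what 63 evaluable patients per arm detect: a standardised difference of about 0.50 at two-sided 0.05 and 80% power.
5. Give an SD with its source if one can be found, and tabulate power over a range of SDs, as in step 4.

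If log NT-proBNP or adjustment for baseline is preferred, the same can be done on that scale, where the ratio of 0.62 needs a log-SD of at most about 0.96. Section 2.11 must then be changed to match.

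The cost is one rewritten paragraph, plus an edit to section 2.11 if the scale or adjustment changes. No extra patients are needed. The downside is that the power the trial can honestly state may become less favourable.

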### Statistical analyses

2.11

The statistical analyses of primary and secondary outcomes will be conducted in both the intention-to-treat set and the per-protocol set. Primary and secondary endpoint data will be collected for the entire follow-up period for all patients. Patients lost to follow-up will be considered at risk until the date of last contact, at which point they will be censored. In the per-protocol set, patients who undergo randomization but withdraw consent to participate or not treated according to the allocated procedure after randomization will be excluded from per-protocol statistical analyses.

IBM SPSS V17.0 software pack was used for data analysis. The normal distribution of the data was tested with Pearson test. Independent sample *t* test was used for the comparison of data with normal distribution, while Spearman test was used for the comparison of data without normal distribution. Data with normal distribution were expressed as arithmetic mean ± standard deviation, while data without normal distribution were expressed as median value (minimum–maximum). A *P* value between .1 and .05 was considered marginally significant, a *P* value between .01 and .05 was considered significant, .001 and .01 highly significant, and < .001 very highly significant.

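### Section 2.7 pairs a type II error of 0.2 with 1.28, the quantile for 0.10, so 63 per arm follows from the printed quantiles but not from the stated error rate

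*Protocol article*

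**What the plan says.** Section 2.7 of the protocol article sizes the trial on NT-proBNP with a superiority formula for two proportions: n per arm = (Uα + Uβ)² × 2P(1 − P)/(P1 − P2)².

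- **Error rates and quantiles:** "Given a type I error rate of α = 0.05", then "type II error rate of β = 0.2, Uα(0.05)=1.65, Uβ (0.2) =1.28". No power figure is printed, so power is given only through β. The section does not say whether α is one-sided or two-sided.
- **Effect:** the reduction under PCI is taken from a previous study as 32%, and 58% is assumed for this trial.
- **Result:** 63 per arm, 126 in total. "Considering a dropout rate of 10%, a total of 138 patients need to be allocated", and the recruitment target is then set at 140.

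Section 2.11 (Statistical analyses) sets the bands for reading P values, among them: "value between .01 and .05 was considered significant". Values between .05 and .1 are called marginally significant. That section does not state sidedness either.

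**The concern.** The label "Uβ (0.2) =1.28" attaches the wrong number to the stated error rate. The two statements about β in one sentence cannot both be right, and nothing else in the article shows which was meant. A reader who takes β = 0.2 at face value will report a design with 80% power. A reader who trusts the quantile will report 90%.

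The value of Uα adds a second ambiguity. The 1.65 in "Uα(0.05)=1.65" is the one-sided 5% quantile, and a one-sided 5% rule corresponds to a two-sided 10% rule. Neither section 2.7 nor section 2.11 says that the test is one-sided. What is at stake is whether the power and success criterion behind 63 per arm can be reported correctly, and whether they match the test that will be run.

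**Working it through.** **Inputs, all from section 2.7 unless marked**

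- P1 = 0.32 and P2 = 0.58, so the difference is 0.26 and its square is 0.0676.
- P = (0.32 + 0.58)/2 = 0.45. This is an assumption, because the text does not define P.
- Printed quantiles: Uα = 1.65, Uβ = 1.28.
- Standard normal values: 1.645 for one-sided 0.05, 1.960 for two-sided 0.05, 0.842 for β = 0.20, 1.282 for β = 0.10.

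**Step 1. Common factor**

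2P(1 − P)/(P1 − P2)² = 2 × 0.45 × 0.55/0.0676 = 0.495/0.0676 = 7.322.

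**Step 2. Reproduce the plan's figure**

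(1.65 + 1.28)² × 7.322 = 8.585 × 7.322 = 62.9, rounded up to 63. The printed figure is reproduced, which supports P = 0.45 and shows that 1.28 was the value actually used.

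**Step 3. What the error rates would require in the same formula**

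| α | β | Calculation | Per arm |
|---|---|---|---|
| one-sided 0.05 | 0.2 | (1.65 + 0.84)² × 7.322 = 45.4 | 46 |
| two-sided 0.05 | 0.2 | (1.96 + 0.84)² × 7.322 = 57.4 | 58 |
| one-sided 0.05 | 0.1 | (1.65 + 1.28)² × 7.322 = 62.9 | 63 |
| two-sided 0.05 | 0.1 | (1.96 + 1.28)² × 7.322 = 76.9 | 77 |

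Only the third row gives 63. Neither row with β = 0.2 does.

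**Step 4. Power that 63 per arm gives**

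Inverting the formula: √(63/7.322) = 2.933.

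- One-sided 0.05: Φ(2.933 − 1.645) = Φ(1.288) = 90.1%.
- Two-sided 0.05: Φ(2.933 − 1.960) = Φ(0.973) = 83.5%.

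A two-proportion calculation that uses separate null and alternative variances gives 90.9% and 84.3%, so the picture does not depend on the pooled-variance form.

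**Step 5. Dropout**

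- 138 × 0.9 = 124.2, below the 126 required.
- 126/0.9 = 140, and 140 × 0.9 = 126. The recruitment target therefore meets the requirement exactly.
- 126 × 1.1 = 138.6, so 138 looks like an add-10% step rounded down.

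**The case against.** The strongest reply is that nothing about the trial's size is harmed. The section prints the quantiles it used, and 63 follows from them. On the plan's assumptions, power exceeds 80% under either sidedness. This stands, and it limits the point to a wrong label and an undeclared sidedness. Three stronger readings might tempt a reader, and the document does not support them.

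- **That the sample size cannot be reproduced, or that the trial is underpowered.** It reproduces from the printed quantiles, and the slip errs towards more patients than β = 0.2 requires. The one exception is conditional: if the sponsor meant 90% power at two-sided 0.05, then 77 per arm are needed and 63 gives 83.5%. The text does not show that intent.
- **That 1.65 is an error because the analysis is two-sided.** Section 2.7 describes a superiority test, with which a one-sided quantile is compatible, and section 2.11 never states sidedness. Reading its P-value bands as two-sided is an inference. The document supports only a request to declare one sidedness for both places.
- **That the dropout slip leaves the trial short.** The shortfall to 124 applies to 138, a number the trial does not use. The target of 140 yields 126.

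One further caution is fair. The formula treats 32% and 58% as proportions, although the text describes them as reductions in a biomarker level. The power figures here hold within the plan's own formula and say nothing about whether that formula suits the endpoint.

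**Conclusion.** The point holds in a limited form. The statement that 1.28 is the quantile for β = 0.2 is wrong, and the 80% power implied by β does not describe 63 per arm. By the plan's formula, with P = 0.45 assumed, the power is about 90% one-sided or about 83.5% two-sided, which is 10 or 3.5 percentage points above the implied value. Against the 63 planned, the stated β would need 17 fewer per arm with the one-sided quantile (46) or 5 fewer with the two-sided one (58).

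This is an error of reporting in a core design parameter and, on the stated assumptions, not a threat to the sample size. It would become one only if 90% power at two-sided 0.05 was the aim: 77 per arm, 154 evaluable, and 154/0.9 = 171.1, so 172 recruited.

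**What to change.** Keep recruitment at 140 and restate section 2.7 in one of two consistent ways:

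1. One-sided α = 0.05 (Uα = 1.65) with β = 0.10 (Uβ = 1.28), power about 90%, 63 per arm.
2. Two-sided α = 0.05 (Uα = 1.96), reporting the power that 63 per arm gives, about 83.5% by this formula (β about 0.165), in place of β = 0.2.

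In either case, define P, and declare in section 2.11 the same sidedness for the test of the primary outcome. The sponsor should choose according to what was intended, since the document does not settle it.

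As a side correction, replace 138 by 126/0.9 = 140.

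The cost is a few words in two sections. No participant numbers or procedures change under either option.

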### Outcome measures

2.8

#### Background information

2.8.1

Background information includes demographic data and general clinical data. Demographic data consists of gender, age, height, weight, and so on. General clinical data consists of medical history, course of disease, treatment history, combined diseases, concomitant medications, and so on. The participants’ information and privacy will be strictly protected and forbidden to the public.

#### Safety outcomes

2.8.2

Safety is assessed by vital signs, laboratory examinations, and AEs. Vital signs include body temperature, breathing, blood pressure, and heart rate. Laboratory examinations include blood, urine and stool routine, liver, and kidney function. AEs will be recorded all the time during the treatment. The development of AEs will also be observed until the adverse reactions disappear.

#### Primary and secondary outcomes

2.8.3

The primary outcome measures of the study are NT-proBNP and left ventricular ejection fraction, which will be measured at baseline and 8 weeks after randomization. Secondary outcomes include plasma levels of microRNA-145, plasma creatine kinase-MB, and CardiaC Troponin I levels in blood samples. At the same time, the trial also observes the occurrence of MACEs defined as the composites of deaths from any cardiac causes, myocardial infarction, and revascularization (PCI or CABG) at 8 weeks after randomization. The efficacy of angina symptoms, Seattle Angina Questionnaire, will be recorded at baseline and 8 weeks after randomization and TCM syndrome efficacy.^[24]^ Items to be measured and the time window of data collection are shown in Table 3.

**Table 3 T3:** Schedule of data collection.

Items	Screening period within 1 wk	Treatment period 4–8 wk	Follow-up period 2–12 mo
Signed informed consent	√		
Inclusion/exclusion criteria	√		
Demographic data	√		
Medical history, course of disease, treatment history	√		
Combined diseases	√		
Concomitant medications	√	√	
LVEF	√	√	
NT-proBNP	√	√	
microRNA-145	√		
CK-MB	√		
cTnI	√		
MACEs			√
SAQ	√	√	
TCM syndrome efficacy	√	√	
Vital signs	√	√	
Blood, urine and stool routine	√	√	
Liver and kidney function	√	√	
Adverse events		√	√

Vital signs: temperature, heart rates, breathing, and blood pressure.

CK-MB = creatine kinase-MB, cTnI = CardiaC Troponin I, LVEF = left ventricular ejection fraction, MACE = major adverse cardiac event, SAQ = Seattle Angina Questionnaire, TCM = Traditional Chinese Medicine.

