**Methods::**

This study is a randomized, double-blinded, placebo-controlled, single-central clinical trial. A total of 140 participants are randomly allocated to 2 groups: the intervention group and the placebo group. Based on routine medications, the intervention group will be treated with YLS and the placebo group will be treated with YLS placebo. All participants will receive a 8-week treatment and then be followed up for another 12 months. The primary outcome measures are N terminal pro B type natriuretic peptide (NT-proBNP) and left ventricular ejection fraction. Secondary outcomes are plasma levels of microRNA-145, plasma cardiac enzyme, and Troponin I levels in blood samples, changes in ST-segment in ECG, Seattle Angina Questionnaire, the efficacy of angina symptoms, and occurrence of major adverse cardiac events. All the data will be recorded in case report forms and analyzed by SPSS V.17.0.

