### Overall objective

2.3

The trial will investigate whether the postoperative administration of YLS in AMI patients treated with PCI will improve cardiac function. And it explores microRNAs (miRNA)-145 as detection of blood-based biomarkers for AMI by evaluating the relation between miRNAs in plasma and cardiac function.

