This trial tried to incorporate miRNA-145 as one of surrogates for hard clinical endpoints. miRNAs are single-stranded RNA molecules 20 to 25 nucleotides in length coded by genes transcribed by DNA, which are known as “noncoding RNA.” While miRNAs are not converted to protein products, they act to gene expression, primarily through translation repression or RNA degradation.^[34,35]^ Several investigations have demonstrated that miRNAs may play a major role in regulating most of the human genome, including gene alterations associated with various aspects of heart disease, such as ischemic MIR.^[36]^ Genetic or pharmacological manipulation of miRNAs has been indicated to modulate the sensitivity of the myocardium to MIR,^[35]^ protective noncoding RNAs may have a role in the setting of anticipated ischemia.^[37]^ Because of their significant role in all stages of MIR, regulating miRNAs is a promising therapeutic strategy. The miRNAs in plasma and serum are reported that are present in a remarkably stable form and can be detected in the peripheral circulation.^[38]^ Therefore, the miRNAs can be considered as promising novel biomarkers for the diagnosis and prognosis of cardiovascular diseases.^[39]^ Previous studies reported that the expression of miRNA-145 is associated with MIR.^[40]^ In animal model of ischemia/reperfusion injury and myocardial hypoxia/reoxygenation-induced cell model, miRNA-145 were significantly reduced,^[41,42]^ which indicated that the abnormal expression of miR-145 may be the good candidate for MIR.

A potential limitation of our study is that the trial will be undertaken in China, it is uncertain whether the similar effects are available to other ethnic groups and regions. To conclude, the aim of this trial is to demonstrate that YLS will protect the myocardial function in patients with AMI after successful PCI and subsequently yield long-term benefit.

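### Three secondary outcomes (miR-145, CK-MB, cTnI) are scheduled at screening only, so they have no defined post-treatment measurement, and section 2.11 contradicts that schedule

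*Protocol article*

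**What the plan says.** Section 2.8.3 of the protocol article gives plasma miR-145, CK-MB and cTnI the status of secondary outcomes: "Secondary outcomes include plasma levels of microRNA-145, plasma creatine kinase-MB, and CardiaC Troponin I levels in blood samples". That sentence has no time point. The timing phrase just before it, "which will be measured at baseline and 8 weeks after randomization", belongs to NT-proBNP and LVEF only. For everything else the section points to the schedule: "Items to be measured and the time window of data collection are shown in Table 3".

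Table 3 has three columns: screening, treatment period (weeks 4 to 8) and follow-up (months 2 to 12). The rows for the three markers carry one tick each, in the first column, headed "Screening period within 1 wk".

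Four other places bear on the point:

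- Section 2.11 says that data on primary and secondary endpoints are gathered throughout follow-up in every patient. It names no visit for any blood marker.
- Section 2.6 sets the start of study treatment: "Once randomized, the patient will receive postoperative administration of either YLS or placebo after reperfusion of the culprit artery, as soon as possible".
- The Discussion (section 3) says: "This trial tried to incorporate miRNA-145 as one of surrogates for hard clinical endpoints".
- Section 2.3 puts the miR-145 objective more narrowly. The marker is to be explored "by evaluating the relation between miRNAs in plasma and cardiac function".

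**The concern.** A secondary outcome in a randomised trial is there to show what treatment does to it, and that needs a value taken at a defined time after treatment starts. Table 3 schedules none for these three markers. A site that follows the table would take no later miR-145 sample, and plasma that was never drawn cannot be recovered at analysis. The trial would then report arm comparisons on three named outcomes that say little or nothing about YLS. One of the three is the biomarker that the article features in its abstract and Discussion.

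**Working it through.** No sample-size or power figure enters this point, so the check sets the printed schedule beside the text.

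**Step 1. Table 3, cell by cell**

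| Item | Status | Screening | Treatment period | Follow-up |
|---|---|---|---|---|
| LVEF | primary | yes | yes | no |
| NT-proBNP | primary | yes | yes | no |
| SAQ | secondary | yes | yes | no |
| MACEs | secondary | no | no | yes |
| miR-145 | secondary | yes | no | no |
| CK-MB | secondary | yes | no | no |
| cTnI | secondary | yes | no | no |

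The table separates single from repeated measurements, and it places a lone tick in the third column for MACEs. The columns therefore survived conversion from PDF, and the empty cells for the three markers are what the article prints.

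**Step 2. Table 3 against section 2.11**

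Table 3 implies no collection of these markers after screening. Section 2.11 implies collection throughout follow-up. Both cannot be true of the same markers. Section 2.11 does not settle the matter, because it gives no visit at which a sample would be drawn.

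**Step 3. What an arm comparison would estimate**

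Let Y be the single scheduled value, A the YLS arm and B the placebo arm.

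- If Y is taken before the first dose, randomisation gives E(Y_A) − E(Y_B) = 0 whatever the drug does. A test at the 5% level then rejects with probability 5%, for any true later effect.
- If some samples in the screening window follow the first dose, the comparison mixes pre-dose values with values at unstated times after it. The contrast then has no defined time to which it refers.

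The documents do not fix which case applies. Table 2 requires AMI within 12 hours, section 2.6 starts treatment promptly after reperfusion, and section 2.10 has baseline characteristics collected no sooner than 24 hours after the procedure. The screening column allows a week. In neither case is there a defined post-treatment value.

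**Step 4. The two miR-145 aims**

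- *Surrogate statement (section 3).* To show that a marker stands in for clinical endpoints under treatment, one must estimate the treatment effect on the marker. No defined post-treatment miR-145 value is scheduled, so this cannot be supported.
- *Objective (section 2.3).* A single early miR-145 value can be related to LVEF and NT-proBNP at baseline and at 8 weeks, both of which are scheduled. That is a diagnostic or prognostic analysis, and it remains possible.

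**Step 5. Count**

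The abstract lists seven secondary outcomes: miR-145, cardiac enzyme, troponin I, ST-segment change, SAQ, angina efficacy and MACE. Three of the seven are affected by the screening-only schedule.

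**The case against.** The best defence is that Table 3 merely lacks ticks. Section 2.11 shows an intention to collect secondary endpoint data during follow-up, and a journal article condenses a fuller protocol. This may well be the explanation. It does not remove the point, because the article does more than leave timing unsaid: it prints a schedule, refers the reader to it, and that schedule conflicts with the status of the markers. What stands is that this is an internal contradiction, and not proof of a settled decision to sample once.

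Four stronger readings are tempting, and the documents support none of them.

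- *That the trial will have no post-randomisation data on these markers.* Section 2.11 points the other way, and the screening window read with sections 2.6 and 2.10 does not show that every sample precedes the first dose. The supportable statement is that no post-treatment time is defined.
- *That the miR-145 work fails altogether.* Only the surrogate sentence in the Discussion is unsupported. The objective in section 2.3 survives in part.
- *That four outcomes are affected, counting ST-segment change.* The abstract lists "changes in ST-segment in ECG" and neither section 2.8.3 nor Table 3 mentions an ECG. That is an omission which a condensed article may leave to the full protocol, and it differs from a printed single time point.
- *That the trial's main conclusion is at risk.* Both primary outcomes are ticked at screening and in the treatment period, and the sample size does not depend on the three markers.

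**Conclusion.** The point holds for three secondary outcomes. As printed, Table 3 gives miR-145, CK-MB and cTnI no defined post-treatment measurement and contradicts section 2.11. If the schedule is followed, arm comparisons on these markers would essentially check baseline balance, and the surrogate statement on miR-145 would have no basis.

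This rests on two things: that Table 3 governs sampling, as section 2.8.3 says, and that no fuller schedule elsewhere overrides it. If later samples are in fact planned, the defect is confined to the text and table, which still need to agree.

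**What to change.** Reconcile section 2.8.3 with Table 3, section 2.11 and section 3, by one of two routes.

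1. **Keep the three as outcomes.** In Table 3, tick miR-145 in the treatment-period column (weeks 4 to 8) and tie it to the 8-week NT-proBNP visit. The table has no separate week-8 column, so the visit should be named. State defined pre-dose and post-dose sampling times for CK-MB and cTnI. Analyse each marker adjusted for its pre-dose value. The cost is one more miR-145 assay per patient, so at most 140 × 1 = 140 for the planned recruitment, plus obtaining and recording the CK-MB and cTnI values. This assumes that the NT-proBNP blood draw can also serve miR-145 and that in-hospital tests can supply the other two. The article confirms neither.
2. **If no later sample is planned, reclassify them.** Call the three baseline prognostic variables, limit the miR-145 analysis to its relation with LVEF and NT-proBNP, and delete the treatment-effect and surrogate claims. This needs no extra sampling, but it gives up any statement about the effect of YLS on these markers.

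Under either route, reword the section 2.11 sentence on endpoint collection so that it agrees with Table 3. As a separate minor correction, bring the abstract's ST-segment outcome into line with section 2.8.3 and Table 3.
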